**Figure 3 f3:**
[figure not shown]
Specialists composing the multidisciplinary team of the FENICE clinical trial. Each BC patient enrolled in the study arm will be evaluated and monthly followed up by specialists before and during the adapted fencing activity.

### Inclusion and exclusion criteria

The inclusion and exclusion criteria for the FENICE trial are listed in **Table 3**.

**Table 3 T3:** Inclusion and exclusion criteria.

Inclusion criteria	Exclusion criteria
The subject, at the time of diagnosis, must be between 18 and 70 years old	Subjects with recurrence of BC and treated with surgery, chemotherapy, radiotherapy, and hormone therapy
Subject affected by non-metastatic BC and treated with surgery for primary tumor	Life expectancy estimated to be less than three months by treating clinical team
Subject is able and willing to take part and be followed-up for at least 24 weeks	Unable and unwilling to consent to the study
Subject can carry out Adapted Physical Activity	Subject is, in the opinion of the Investigator, not suitable to participate in the study (e.g. surgical outcomes, severe co-morbidities, osteoporosis)
Subject has signed informed consent	Patient has existing impaired hepatic, renal or cardiorespiratory, Lymphatic function for which Adapted Physical Activity is contraindicated

### Recruitment and study population

Patients of any ethnicity who are at least 18 years old with diagnosis of non-metastatic BC and already treated with surgery for primary tumor are eligible. The recruiting physicians will check the in- and exclusion criteria and determine whether the patient is eligible for participation (see **Table 3**). Participation in the FENICE study is on a voluntary basis. Participants will be informed about the aims of the study both verbally and in writing and will have the opportunity to ask questions and refuse participation.

### Ethical considerations

The study will determine which group between subjects practicing APA and following Mediterranean diet (study arm) and those following the normal BC guidelines (standard of care) will benefit the most. Written informed consent, approved by an Italian Ethics Committee (R.S 100.23 5^th^ May 2023), will be obtained from each participant. Health complications for the participants will be addressed by the multidisciplinary team involved in the research and, if necessary, by contacting the patients’ MMG. If any complications that endanger the patient’s health, should arise the participant will be asked to withdraw from the study. Finally, subjects can leave the study at any time for any reason without any consequences, and, likewise, the research physicians can decide to withdraw a subject from the study for urgent medical reasons.

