### Design of FENICE trial

The FENICE study is a mono-center, randomized clinical trial targeting women with stages I-III BC within four weeks from surgery, conducted at the Breast Unit of Policlinico Tor Vergata Rome and Frascati Scherma ASD. The sequence of study and control group is randomized to minimize the influence of time-dependent variables. The participants, regardless of arm dominance, will be followed up by oncologists, radiotherapists, and surgeons according to the BC guidelines. All subjects participating in the study will undergo a sports medicine examination to objectify whether there are any alterations or diseases that pose a risk to the patient and to determine whether the patient needs to have additional tests and more specific examinations performed. For participants in the study arm only, APA consists of two fencing sessions (1 h/session) per week within 15 days of enrollment. The minimum number of sessions for the assessment of the primary endpoint is 48 sessions over six months up to a maximum of 96 sessions over 12 months (**Figure 2**).

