**Figure 2 f2:**
[figure not shown]
Study design of the mono center randomized FENICE clinical trial. All screened patients will receive a complete clinical, psychological, and instrumental evaluation, (lifestyle, comorbidities, oncological treatments and their related sequelae and AEs). Participants in the control arm will receive the usual recommendations based on the good clinical practice guidelines and according to 1) the stage of BC disease; 2) planned oncological treatments; 3) sequelae and AEs caused by oncological treatments. In the study arm, participants will be treated with the usual clinical and therapeutic recommendations together with APA and correct lifestyle suggestions (Mediterranean diet). All participants will be followed up for a minimum of 12 month, and up to a maximum of 24 months.

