### Follow up visits

Participants will be included in the FENICE study for a total of 24 months and will be followed up differently based on the inclusion arm. In the study arm (APA and Mediterranean diet arm) patients will be monthly followed up for comorbidities, co-medication and herbal remedies, adverse events, and body mass index (BMI). Moreover, every three months also clinical evaluation, blood parameters, instrumental exams and QoL questionnaires will be carried out for the study arm patients. In the control arm, instead, all the mentioned parameters will be followed up every three months (see **Figure 2**).

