### Data collection

Participants will be included in the study and will undergo several follow-up visits. During the follow-up period trained research nurses/data managers will contact patients at baseline (T=0) (± one week), and subsequently every four weeks (± two weeks), to go through a standardized questionnaire and to collect data on the outcomes of sequelae and clinical symptoms/AEs. In addition, all patients will be contacted by the research nurse/data manager at the end of the APA period (± two weeks from the end) to complete a last questionnaire. Research nurses/data managers additionally will collect required laboratory and or test results from participants’ (electronic) medical records. If a subject discontinues the APA and lifestyle interventions during the 12-week follow-up period, follow-up will continue.

The questions within the surveys will be performed to assess the occurrence and severity of any new symptoms experienced by the participants, and the global physical and psychological health after the beginning of APA. The questionnaires that will be administered to participants during the study period are listed in **Table 4**.

**Table 4 T4:** Type of questionnaire that will be administered to breast cancer patients.

Objective	Questionnaire
**Disability**	The DASH (disabilities of the arm, shoulder, and hand measurement tool) questionnaire
**QoL**	EORTC qlq-C30 and EORTC qlq- BR23 questionnaire
**Fatigue**	The MFI 20 (Multidimensional fatigue inventory) questionnaire
**Anxiety-depression**	The HADS (Hospital anxiety and depression scale) questionnaire
**Physical activity and sedentary behavior**	The short version of the IPAQ (international physical activity questionnaire)
**Oedema assessment**	Disability scale for oedema

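### Women with health-endangering complications are asked to leave the study itself, and the only promise of follow-up after stopping the intervention is tied to a 12-week period that fits no other stated duration

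*Protocol article*

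**What the plan says.** The Ethical considerations section sets up two tiers. In general, "Health complications for the participants will be addressed by the multidisciplinary team involved in the research". For complications that endanger health there is a separate rule: if any "should arise the participant will be asked to withdraw from the study". In addition, "the research physicians can decide to withdraw a subject from the study for urgent medical reasons". Both exits are from the study. Neither sentence mentions stopping fencing while questionnaires and adverse-event follow-up go on.

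Data collection contains the only rule for women who stop the intervention: "If a subject discontinues the APA and lifestyle interventions during the 12-week follow-up period, follow-up will continue".

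The other durations are:

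- Design of FENICE trial: "The minimum number of sessions for the assessment of the primary endpoint is 48 sessions over six months up to a maximum of 96 sessions", the maximum being spread over 12 months.
- Figure 2 legend: "All participants will be followed up for a minimum of 12 month, and up to a maximum of 24 months".
- Follow up visits: "Participants will be included in the FENICE study for a total of 24 months".
- Table 3, inclusion criteria: "Subject is able and willing to take part and be followed-up for at least 24 weeks".

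The Primary objective section counts a reduction in the number and severity of adverse events as part of the overall improvement to be shown. The Sample size section rests on the DASH score.

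**The concern.** A woman whose complication endangers her health has, by definition, had an event of the kind the primary objective counts. If she then leaves the study, what happens to her afterwards goes unobserved: the course of that event, later events and later DASH scores. The reason for the missing data is tied to the outcome, so the loss is informative. The women who remain are a selected group, and recruiting more women does not correct for that.

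The rule that could protect against this is the one in Data collection, which already treats stopping the intervention as different from leaving follow-up. Its stated time frame, however, ends well before the primary endpoint can be assessed. It therefore gives no assurance for women who stop between week 12 and the endpoint, and it does not say how it fits with the study-withdrawal rule for women who stop because of a complication.

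**Working it through.** **1. The durations side by side**

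| Source | Duration | 12 weeks as a share |
|---|---|---|
| Data collection | 12 weeks | – |
| Inclusion criterion | 24 weeks | 12/24 = 50% |
| Design, minimum sessions | 6 months (about 26 weeks) | 12/26 = 46% |
| Design, maximum sessions; Figure 2 minimum follow-up | 12 months (52 weeks) | 12/52 = 23% |
| Follow up visits; Figure 2 maximum | 24 months (104 weeks) | 12/104 = about 12% |

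The earliest primary assessment comes after 48 sessions at two a week, 48/2 = 24 weeks, or about 26 weeks if six calendar months are meant. The 12-week period ends 12 to 14 weeks before that. It matches none of the other durations.

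**2. The plan's own sample size**

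Inputs from the Sample size section: difference 15 DASH points, SDs 20 and 10, alpha 0.01, beta 0.01. Two-sided normal approximation:

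n = (2.576 + 2.326)² × (20² + 10²) / 15² = 24.03 × 500/225 = 53.4, so 54 per group.

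With the noncentral t distribution the result is 56 per group (power 0.990), which reproduces the stated figure. Enrolling 75 per group leaves room for 1 − 56/75 = 25.3% loss. Power is not the difficulty: at 40% loss (45 per arm) it is still 96.5% at alpha 0.01.

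**3. What informative loss could do (illustration)**

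The documents give no complication or withdrawal rate and no link between withdrawal and DASH. The loss fractions, score gaps and correlations below are assumptions. So is the restriction of loss to the study arm and an analysis of completers only.

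*Simple version.* If a fraction d is lost and those women would have scored g points worse than completers, the completers' mean is too favourable by d × g.

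- d = 5%, g = 10: 0.05 × 10 = 0.5 points
- d = 25%, g = 20: 0.25 × 20 = 5.0 points

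*Selection version.* Suppose the women lost are those with the highest complication tendency, and that this tendency correlates ρ with a worse DASH result. The shift is then ρ × SD × φ(z)/(1 − d), where z is the normal quantile at 1 − d and φ the normal density. With SD = 20:

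- ρ = 0.3, d = 5%: 0.3 × 20 × 0.103/0.95 = 0.65 points; d = 25%: 0.3 × 20 × 0.318/0.75 = 2.5 points
- ρ = 0.5, d = 5%: 1.1 points; d = 25%: 4.2 points

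The standard error of the difference is √(400/[75(1 − d)] + 100/75), which is 2.64 at 5% loss and 2.91 at 25%. With no true effect, the chance of a significant result at the protocol's 0.05 threshold rises to about 6% to 14% for ρ = 0.3 and 7% to 31% for ρ = 0.5.

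*Loss in both arms.* In the selection version, equal loss leaves a net shift of half the above, 0.3 to 2.1 points, because the assumed SDs are 20 and 10. In the simple version, equal loss with an equal gap cancels.

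**The case against.** Several stronger readings are tempting, and the documents do not support them.

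- A reader might infer that follow-up ends for anyone who stops after week 12. Data collection does not say so. The Figure 2 legend and Follow up visits promise 12 to 24 months in general terms, and Data collection has all patients contacted at the end of the activity period. The 12-week phrase may simply be a wrong duration. That objection stands: later follow-up is not cut off by this sentence, but neither is it protected, since the general durations carry no rule for women who stop or are withdrawn.
- A reader might infer that any health complication leads to withdrawal. Only those that endanger health do; the team manages the others.
- A reader might infer that the worst adverse events vanish from the data. The event that triggers withdrawal is known at the time and can be recorded. What is lost is what follows.
- A reader might infer that loss must be greater in the study arm. The withdrawal rule applies to both arms and no rate by arm is given. Only the study arm fences and Follow up visits reviews it monthly against three-monthly for controls, which makes an imbalance plausible. On the other side, Data collection describes four-weekly contact without distinguishing arms, and participants are medically screened with individually set exercise intensity.
- A reader might take the whole 25.3% margin as expected loss. The protocol states no dropout rate and attributes the larger sample partly to its enrolment capacity.

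The article also states no completers-only analysis, and analysis sets may be defined in a document not shown. That limits what can be said about the eventual estimate. It does not help with outcomes that are never collected.

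**Conclusion.** The point holds in a limited form. Followed as written, the Ethical considerations section ends DASH and adverse-event collection after a health-endangering complication, and that loss is informative because the trigger belongs to the primary objective. The 12-week wording in Data collection cannot be reconciled with the other durations and leaves follow-up after later discontinuation unprotected.

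The direction and size of any bias cannot be derived from the documents. Under the stated assumptions, with 5% to 25% lost in the study arm only, the completers' mean could shift by roughly 0.5 to 5 DASH points towards the intervention. That is 0.5/15 = 3% to 5/15 = 33% of the planned difference, with the upper end a worst case. It would be less if both arms lose women. The textual findings are firm; the consequences are an inference.

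**What to change.** Separate data collection from treatment decisions. State that DASH and adverse-event collection continues through the last scheduled visit, in both arms, for every randomised woman, whenever and for whatever reason the intervention stops, unless she withdraws consent to follow-up. Make the Ethical considerations and Data collection sections say the same thing on this.

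Reconcile the 12-week wording with the Design section, the Figure 2 legend, Follow up visits and the 24-week inclusion criterion, and state one follow-up duration throughout.

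Whether and when the intervention stops for a complication remains a clinical matter for the investigators, and nothing here bears on it. The cost is protocol and consent wording, plus telephone questionnaires for a minority of women. No change in sample size is needed.

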### Follow up visits

Participants will be included in the FENICE study for a total of 24 months and will be followed up differently based on the inclusion arm. In the study arm (APA and Mediterranean diet arm) patients will be monthly followed up for comorbidities, co-medication and herbal remedies, adverse events, and body mass index (BMI). Moreover, every three months also clinical evaluation, blood parameters, instrumental exams and QoL questionnaires will be carried out for the study arm patients. In the control arm, instead, all the mentioned parameters will be followed up every three months (see **Figure 2**).

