### Primary objective

The primary objective of the study is to compare whether implementation of an APA and healthy lifestyle (Mediterranean diet) will result in an overall improvement of physical and mental status including reduction in the number and severity of clinically relevant adverse events (AEs), in the study group compared with the control group during a 24-month enrollment period.

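### Adverse events, part of the primary objective, are scheduled monthly in the study arm but three-monthly in controls, and a second section conflicts with this, so ascertainment may be unequal

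*Protocol article*

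**What the plan says.** The Primary objective section makes AEs a comparative outcome. The hoped-for overall improvement is described as "including reduction in the number and severity of clinically relevant adverse events (AEs), in the study group compared with the control group".

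The Follow up visits section states that participants "will be followed up differently based on the inclusion arm". In the study arm, "patients will be monthly followed up for comorbidities, co-medication and herbal remedies, adverse events, and body mass index (BMI". For controls: "In the control arm, instead, all the mentioned parameters will be followed up every three months". The stated length is 24 months. The Figure 2 caption gives a minimum of 12 and a maximum of 24.

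The Figure 3 caption ties a further layer of contact to one arm: "Each BC patient enrolled in the study arm will be evaluated and monthly followed up by specialists before and during the adapted fencing activity". No counterpart is described for controls.

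The Data collection section describes something different. Research nurses or data managers contact patients at baseline and "subsequently every four weeks (± two weeks), to go through a standardized questionnaire", and "to collect data on the outcomes of sequelae and clinical symptoms/AEs". No arm is named. The same paragraph refers to a 12-week follow-up period, so it is unclear whether these contacts run for the full 24 months.

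**The concern.** When AE counts are an efficacy outcome, both arms need the same opportunity to report. An event that starts and resolves between two visits is recorded only if the woman still remembers it and is asked about it. With a three-month gap more such events are lost than with a one-month gap. On the visit schedule as written, the study arm would therefore show more AEs than controls even if the true rates were equal, and a real reduction could be masked or reversed.

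Severity may be affected too. A longer gap tends to keep the lasting or memorable events, so the mix of recorded events may differ between arms. The article gives nothing from which to quantify this.

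The schedule is fixed at the point of data collection. Events that were never asked about cannot be recovered by any later analysis.

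**Working it through.** **The plan's own figure.** The only calculated figure is the DASH sample size (Sample size section): difference 15, SDs 20 and 10, alpha and beta 0.01.

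- Two-sided normal formula: n = (20² + 10²)(2.576 + 2.326)² / 15² = 500 × 24.03 / 225 = 53.4, so 54 per group.
- Two-sided noncentral t: 56 per group, power 99.0 to 99.1%. This matches the stated 56.
- 2 × 56 = 112, and 150 leaves (150 − 112)/150 = 25.3% for withdrawal.

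No AE quantity enters this calculation, so the present point does not touch it.

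**Step 1: assessments under Follow up visits.** Study arm: 24/1 = 24 over 24 months, or 12 in one year. Control arm: 24/3 = 8, or 4 in one year. The ratio is 3:1.

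**Step 2: what that could do to recorded counts.** The article gives no AE rate, duration or recall period, so this step is illustrative. Assume equal follow-up, and that an event is recorded only if a scheduled assessment falls within L months of its onset. Then capture = min(1, L/interval). The last column assumes a true rate ratio (study/control) of 0.70, multiplied by the capture ratio.

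| L (months) | Study capture | Control capture | Recorded ratio if true rates are equal | Recorded ratio if true ratio is 0.70 |
|---|---|---|---|---|
| 0.5 | 0.50 | 0.17 | 3.0 | 2.1 |
| 1 | 1.00 | 0.33 | 3.0 | 2.1 |
| 2 | 1.00 | 0.67 | 1.5 | 1.05 |
| 3 or more | 1.00 | 1.00 | 1.0 | 0.70 |

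**Step 3: the same in weeks, with duration and recall separated.** Capture = min(1, (duration + recall)/gap), with gaps of 4 and 13 weeks. For a 4-week event, study-arm capture is 1.00 throughout. Control-arm capture is:

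- no recall: 4/13 = 0.31, ratio 3.2;
- 4 weeks' recall: 8/13 = 0.62, ratio 1.6;
- 8 weeks' recall: 12/13 = 0.92, ratio 1.08;
- 9 weeks' recall or more: 13/13 = 1.00, ratio 1.0.

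A 12-week event with no recall also gives 12/13 and a ratio of 1.08. Both versions span 1.0 to about 3.

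**Step 4: the two sections side by side.**

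- *Follow up visits governs.* AE assessments are 3:1, and Steps 2 and 3 apply.
- *The Data collection contact covers both arms and is the only source for the comparison.* The schedule is 1:1 and the capture ratio is 1.0 for every L.
- *That contact covers both arms, but visit findings are counted as well.* The study arm keeps its extra monthly visits. If contacts are on time, events with L of four weeks or more are caught in both arms. The residual imbalance then concerns shorter events and whatever the additional specialist review brings out.

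The article does not say which of these holds.

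**The case against.** The strongest reply is that the Data collection section, read plainly, already gives every patient the same four-weekly AE questionnaire. That stands, and it makes the finding conditional. A reader might infer from the visit schedule alone that the AE comparison is biased outright. The article does not support that, because a second section describes equal contact.

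It can also be said that this is a condensed article, that Follow up visits refers to Figure 2, which is not shown, and that the source feeding the AE comparison may be settled elsewhere. This is fair as to the source, which is not counted here as an omission. It does not remove the conflict between two sections of the published text. The wording of Follow up visits also presents the difference between arms as intended.

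Third, the objective concerns clinically relevant AEs, and Table 1 lists effects such as lymphedema, arthralgia, peripheral neuropathy and limited shoulder mobility. Many of these may outlast a three-month gap, and the ratio is then near 1.0. This also stands: the upper end of the range applies only to short, poorly recalled events.

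Fourth, AEs are one part of a broad objective, the trial is sized on DASH, and the bias in counts runs against the intervention, so it would not manufacture a reduction in AE counts. All true. Hiding a genuine reduction would still defeat that part of the objective.

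A reader might also want a probability of a falsely significant AE difference. The article cannot supply one. It would depend on an assumed event rate, an assumed capture ratio and an assumed between-patient variation in counts.

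**Conclusion.** The point holds in conditional form. Follow up visits sets AE assessment at 24 against 8 over 24 months for an outcome that belongs to the between-arm primary objective, and Data collection conflicts with it. If the first section governs, or if the extra study-arm visits feed the comparison, short-lived AEs are over-represented in the study arm and the count comparison is biased against the intervention.

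The 3:1 schedule follows directly from the text. The effect on recorded rates does not: 1.0 to about 3 is a range under assumed durations and recall, with equal true rates. An effect on severity is plausible but unquantified. The DASH calculation reproduces and is not affected. Because missed events cannot be recovered, the conflict should be settled before AE follow-up data accumulate.

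**What to change.** Reconcile Follow up visits with Data collection. State that the four-weekly nurse or data-manager contact, with the same questionnaire and the same recall window, is the AE source in both arms for the whole follow-up. Clarify the 12-week reference in Data collection accordingly. Base the between-arm comparison of AE number and severity on that common contact only. Report AEs found only at the additional study-arm specialist visits for safety, outside the comparison.

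The cost is a wording change. If the four-weekly contact was not meant to include controls, or not for the full period, brief additional calls to control patients are also needed. Sample size does not change.

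A cheaper-looking alternative is to compare only events recorded at the three-monthly visits common to both arms. This should not be used unless both arms are asked about the full three months. Study-arm women will already have reported earlier events at their monthly visits, so their three-monthly visit could cover about one month of new events against three in controls. That would turn the bias in favour of the intervention.
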